**Objective:**

The objectives of this study are to (1) assess the current oral hygiene knowledge, attitude, and behavior and identify barriers and facilitators for implementing the oral health education training package among AWWs, parents, and other key stakeholders; (2) evaluate the oral health education training package for coverage, acceptability, adoption, fidelity, and scalability; and (3) assess the impact of an oral health education training package on the improvement in oral health knowledge, attitude, and behavior among mothers.

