Few studies have explored the effectiveness of oral health promotion by AWWs in India [16-20], but the focus on implementation parameters has been limited. This study addresses a critical gap by evaluating a model for integrating oral health into community-based maternal and child health services through Anganwadi centers**.** This study is an implementation research project aimed at evaluating the feasibility and implementation of an oral health education training package delivered through AWWs using the Exploration, Preparation, Implementation, and Sustainment (EPIS) framework. Changes in oral health knowledge among mother-child dyads will be assessed as secondary exploratory effectiveness outcomes. The objectives of this implementation research are as follows:

To assess the current oral hygiene knowledge, attitude, and behavior and identify barriers and facilitators for implementing the oral health education training package among AWWs, parents, and other key stakeholdersTo evaluate the oral health education training package for coverage, acceptability, adoption, fidelity, and scalabilityTo assess the impact of an oral health education training package on the improvement of oral health knowledge, attitude, and behavior among mothers

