Adoption	Total number and duration of sessions conducted by each center	Number, hours	—^b^
Fidelity	Proportion of Anganwadi centers adhering to the training module as originally outlined in the manual and training sessions	Direct observation by field assistants	Good: >50% of centers Poor: <50% of centers

^a^AWW: Anganwadi worker.

^b^Not applicable.

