### Data Analysis

Data analysis will be undertaken in line with the sequential mixed methods design of the study, with quantitative and qualitative findings analyzed separately and subsequently integrated to inform intervention adaptation and refinement of implementation strategies.

#### Phase 1

Descriptive statistics will be used to summarize participant baseline characteristics and outcome measures. Continuous variables, such as oral health knowledge, attitude, and behavior scores, will be reported as means and SDs or medians and IQRs, as appropriate. Qualitative data will be transcribed verbatim, translated where required, and analyzed using a thematic analysis approach. Coding will be conducted iteratively, with themes developed across stakeholder groups. Data will be managed using QDA Miner Lite (Provalis Research).

#### Phase 2

Implementation outcomes, including coverage, acceptability, adoption, fidelity, and scalability, will be calculated based on criteria described in Table 1 and expressed as frequency and percentages.

#### Phase 3

To evaluate changes between preintervention and postintervention assessments, linear mixed effects regression models will be used. Time (preintervention assessment vs postintervention assessment) will be included as a fixed effect. Random intercepts will be specified for both Anganwadi centers and individual participants to account for clustering of participants within centers and within-participant correlation arising from repeated measurements. Maternal age, education level, and occupation variables will be included as fixed effects where appropriate to adjust for possible confounding. Knowledge, attitude, and behavior scores will be analyzed as separate outcome variables. Missing data will be assessed for extent and pattern. Mixed effects models allow the inclusion of participants with incomplete outcome data under the missing at random assumption. If substantial missing data are observed, sensitivity analyses using multiple imputation will be considered. Effect estimates will be reported with 95% CIs, and statistical significance will be set at *P*<.05. Analysis will be done using SPSS software (version 22; IBM Corp).

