## Results

The grant application was approved in May 2024, following which the regulatory approvals were obtained. A total of 101 AWWs, representing their respective Anganwadi centers, were enrolled in the study. Needs assessment meetings were held in April 2025. Baseline data collection (July-August 2025) has been completed among selected AWWs, mothers, and ICDS officials using questionnaires, FGDs, and in-depth interviews.

Findings from the formative qualitative phase informed the contextual adaptation and development of the oral health training manual for AWWs. Subsequently, 91 (90.1%) AWWs from Anganwadi centers in Ernakulam district completed a centralized 3-day training program conducted by dental experts (September 2025). IEC materials and oral health manuals were distributed to all trained AWWs.

As of February 2026, the trained AWWs are actively delivering oral health education to mothers and preschool children at their respective centers. Ongoing monitoring and evaluation of implementation outcomes, including coverage, adoption, and fidelity, are underway. The study team anticipates completion of all study phases by April 2026, followed by analysis in May 2026 and completion of a detailed report and manuscript writing by July 2026. Dissemination through conference presentations and stakeholder policy briefings is also expected between June and July 2026.

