## Discussion

### Expected Outcome

The proposed study is expected to provide important evidence on the implementation and effectiveness of an oral health education training package delivered through AWWs. The ICDS program, launched in 1975 by the Government of India, was envisioned as a comprehensive initiative to address the health, nutrition, and early education needs of children aged younger than 6 years, along with pregnant and lactating women. AWWs are the cornerstone of this initiative, serving as community-based agents of change.

However, as far as the introduction of a new component (oral health promotion) is concerned, several practical and operational considerations must be acknowledged in the planning and execution of this intervention to ensure its success and scalability. AWW service delivery is influenced by a complex interplay of means, opportunity, and motives [29], which can help contextualize many of the practical barriers anticipated in this study.

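### Objective 3 promises impact, but the uncontrolled pre-post model can show only change, and the listed covariates do not adjust the time effect for confounding

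*Protocol article*

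**What the plan says.** The third objective, in the Abstract, is to "assess the impact of an oral health education training package on the improvement in oral health knowledge, attitude, and behavior among mothers"; the Introduction repeats it almost word for word. The Phase 3 heading in Methods also speaks of impact. The Discussion (Expected Outcome) says the study is "expected to provide important evidence on the implementation and effectiveness of an oral health education training package", and the Discussion section on monitoring and data validity again refers to the intervention's impact.

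The Introduction also carries a qualifier: "Changes in oral health knowledge among mother-child dyads will be assessed as secondary exploratory effectiveness outcomes".

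The analysis is in Data Analysis, Phase 3. It is a linear mixed model with random intercepts for center and mother. On the exposure it says: "Time (preintervention assessment vs postintervention assessment) will be included as a fixed effect". On adjustment it says: "Maternal age, education level, and occupation variables will be included as fixed effects where appropriate to adjust for possible confounding". No control group, untreated period or repeated baseline is described. The Phase 3 section of Methods states that the Phase 1 questionnaire is used again.

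**The concern.** The wording and the analysis answer different questions. Impact and effectiveness are causal terms: they compare what happened with what would have happened without the package. The model estimates only how far scores moved between two dates. Anything else that moved scores in that interval is inside the same coefficient. Plausible candidates are calendar trend, having seen the same questions before, and health messages from other sources.

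The covariate sentence makes this harder to see. It tells the reader that confounding has been dealt with, when the three variables named describe differences between mothers and the estimate is a difference within mothers. At stake is the sentence the final report may write about objective 3. Under the Phase 3 section, these findings go to program officials to support integration into routine services.

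**Working it through.** **Inputs.** From Sample Size: about 1500 to 3000 children and their mothers, a subsample of about 10%, paired measurements, effect size 0.4 to 0.5, 80% power, 5% significance. Sidedness is not stated; two-sided is assumed. From Results: baseline in July-August 2025, training in September 2025, and completion expected by April 2026, so up to about 8 to 9 months between the two measurements. There are 101 centers.

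**The plan's own figure.** The subsample is 0.10 × 1500 = 150 to 0.10 × 3000 = 300 mothers. The pairs needed are n = ((1.96 + 0.84)/d)², with d in SDs of the change score. This gives 50 at d = 0.4 and 32 at d = 0.5 (52 and 34 with the t distribution). With 150 mothers, power at d = 0.4 is Φ(0.4 × √150 − 1.96) = Φ(2.94) = 99.8%. The claim that the sample is sufficient is confirmed. The point here does not depend on it.

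**What the time coefficient contains.** Write the score of mother i in center j at time t as

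Y = β₀ + β₁·time + γ′X + center effect + mother effect + error,

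with X holding age, education and occupation. Post minus pre for one mother is

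D = β₁ + (error at post − error at pre).

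- X, the center effect and the mother effect do not depend on time, so they cancel.
- β₁ is the package effect plus the drift. Nothing in the design supplies a second equation to separate the two.

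**Check of the covariates.** The planned model was fitted to simulated data for 150 mothers, with and without three covariates constant over time.

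- Complete pairs: in all six data sets the time estimate and its standard error agreed to four decimals (for example 0.2258, SE 0.0870, both ways).
- 20% of post scores missing at random: the largest shift in six data sets was 0.3098 − 0.2967 = 0.013, against standard errors of about 0.08 to 0.10.

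Some fits gave convergence or boundary warnings. The complete-pair result does not rest on them, because the cancellation above is algebraic.

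**How little drift is enough.** Set the package effect to zero. The drift, in SDs of the change score, that gives P<.05 with 80% probability is 2.80/√n:

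- n = 150: 2.80/12.25 = 0.229
- n = 300: 2.80/17.32 = 0.162

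If a between-center share of 0.2 of the variance of change is assumed, and the standard error reflects it, the design effect is 1 + (n/101 − 1) × 0.2. This is about 1.1 at n = 150 and 1.4 at n = 300:

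- n = 150: 2.80 × √(1.1/150) = 0.24
- n = 300: 2.80 × √(1.4/300) = 0.19

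The probability of P<.05 for assumed drifts, without clustering and with no package effect, is:

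| Drift (SD of change) | n = 150 | n = 300 |
|---|---|---|
| 0.1 | 23% | 41% |
| 0.2 | 69% | 93% |
| 0.3 | 96% | over 99% |

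Simulation agreed with these figures, and the mean estimate equalled the drift in full (0.20 for a drift of 0.20). The documents give neither a drift size nor an intracluster correlation, so these figures are illustrative.

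**The case against.** The strongest reply is that the study is an implementation project and says so. The Introduction calls the knowledge outcomes secondary and exploratory, and the Phase 3 analysis text itself speaks of changes between two assessments. The Dissemination section makes the proposal for routine adoption depend on favorable implementation outcomes. All of this stands and limits the severity. A reader might infer that adoption turns on the pre-post P value; the documents do not say that, although Phase 3 findings are shared with officials to support integration. But an exploratory label speaks to priority, not to attribution, and the causal words remain in the same documents.

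A second reply is that the covariates are not useless. The plan keeps mothers with incomplete data under missing at random, and there they can alter the time estimate a little. That is correct. The error is the reason given for including them, not their inclusion.

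Three stronger readings are tempting and are not supported:

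- **Regression to the mean as a source of the change.** This shifts a group mean when people are chosen for extreme scores, and no selection on score is described.
- **Untrained centers as a ready contrast.** Results reports that "91 (90.1%) AWWs from Anganwadi centers in Ernakulam district completed a centralized 3-day training program", which leaves 101 − 91 = 10. It does not say that those centers delivered nothing or supplied follow-up scores.
- **Session counts as a way to settle attribution.** Table 1 does record "Total number and duration of sessions conducted by each center", but delivery is flexible and the Discussion expects motivation to vary, so dose is chosen by the worker and confounded. Leaving such a term out of a condensed article is not an error.

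**Conclusion.** The point holds as a mismatch between claim and analysis. The planned model estimates pre-post change; it cannot support a statement of impact or effectiveness, and age, education and occupation do not adjust the time effect for confounding. This rests on the same mothers being measured twice, which the participant intercepts and the paired sample-size basis indicate, and on the three covariates being essentially constant over 8 to 9 months.

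The size is conditional. If drift of roughly 0.16 to 0.24 SD of the change score occurred (the span with and without the assumed clustering), a null package would usually appear to work. That is about half or less of the 0.4 to 0.5 the plan aims to detect. A reader might infer that drift of this kind is present, or that any improvement seen will be false. The documents do not show that. Drift may be nil, or negative and hide a real effect. What is established is that the two cannot be told apart. It should be corrected, at moderate priority given the exploratory status of the outcomes.

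**What to change.** Three changes of wording, to be carried into the analysis plan and the final report:

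1. State objective 3 and its conclusion as pre-post change in knowledge, attitude and behavior scores, and drop impact and effectiveness for this outcome.
2. Replace the confounding rationale with what the covariates do: support the missing-at-random assumption when follow-up is incomplete, and describe differences between mothers.
3. State as a limitation that, without a comparator, the change cannot be attributed to the package, naming calendar trend, retesting with the same questionnaire and other health messages.

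No new data or model is needed. The cost is a weaker headline claim. An analysis by sessions delivered per center is optional; if reported, it should be labelled exploratory and observational, because workers choose the dose. It does not replace the three changes.

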**Mothers or caregivers**
Mothers or primary caregivers whose preschool children (aged 1-6 years) are enrolled beneficiaries of any Anganwadi center in Kochi Urban III administrative region and who are able to attend Anganwadi sessions and provide informed consent

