### Sample Size

A total of 101 Anganwadi centers in the Kochi Urban III administrative region that include the field practice area of the implementing institution, will be selected. Each Anganwadi unit typically covers about 1000 people, of whom about 15 to 30 are children. The intended beneficiaries of the project would be approximately 1500 to 3000 children and their mothers directly, and about 6000 family members indirectly. The Anganwadi centers hold regular contact sessions (at least twice monthly) with the mothers and families of these children. Thus, the project envisions improving awareness and practices in oral health as a cascading effect from AWWs to children and mothers and ultimately to their families and community.

For the assessment of change in oral health knowledge among mothers, a subsample of approximately 10% of mothers of enrolled children will be selected for the pre-post assessment. This sample size is expected to be sufficient to detect a moderate improvement in knowledge scores (effect size approximately 0.4-0.5) with 80% power at a 5% significance level in paired measurements. As participants are clustered within Anganwadi centers, the analysis will account for clustering using cluster-adjusted statistical methods (eg, mixed effects models or cluster-robust SEs).

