### Constraints With Participation of Mothers

Mothers, the primary beneficiaries of the program, may have difficulty attending sessions due to domestic responsibilities, work obligations, or low prioritization of oral health. In a community-based controlled trial involving Anganwadi centers, it was shown that embedding health education into existing sessions improved reach and impact [19]. Therefore, this study will integrate oral health education into existing touchpoints such as immunization days and monthly mother-AWWs meetings to optimize attendance.

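### The only missing-data sensitivity analysis named for Phase 3, multiple imputation, in its standard form shares the mixed model's missing-at-random assumption, so agreement between the two would not show robustness

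*Protocol article*

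**What the plan says.** All of the missing-data text is in the Data Analysis section of the protocol article, under Phase 3. It has three parts.

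- A descriptive step: "Missing data will be assessed for extent and pattern".
- The basis of the main analysis: "Mixed effects models allow the inclusion of participants with incomplete outcome data under the missing at random assumption".
- The sensitivity analysis: "If substantial missing data are observed, sensitivity analyses using multiple imputation will be considered".

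The model has time as a fixed effect and random intercepts for center and participant. On covariates the section says: "Maternal age, education level, and occupation variables will be included as fixed effects where appropriate to adjust for possible confounding". No attendance or engagement variable is named for the model or the imputation, and no analysis that departs from missing at random is named.

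Two other places bear on the point. The Discussion, under Constraints With Participation of Mothers, expects that mothers "may have difficulty attending sessions due to domestic responsibilities, work obligations, or low prioritization of oral health". The eligibility criteria restrict the sample to mothers or caregivers "who are able to attend Anganwadi sessions and provide informed consent".

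**The concern.** A sensitivity analysis for missing data should vary the assumption that the main analysis cannot check. Here that assumption is that, given the baseline score and covariates, mothers without a post score changed as much as similar mothers who have one. A likelihood-based mixed model relies on it. Standard multiple imputation from the same variables relies on it too and targets the same quantity. The two will therefore agree closely whether or not the assumption is true, and a reader could take that agreement as reassurance.

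The mechanism of interest is simple. A mother who gives oral health little priority may learn little and may also be harder to reach for the post questionnaire. Age, education and occupation would not fully capture that. Both analyses would then credit her with the gain of comparable mothers who stayed. What is at stake is the size of the reported improvement, which the article intends to present to program officials in support of routine integration.

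**Working it through.** **Inputs from the article.** The Sample Size section says that "a subsample of approximately 10% of mothers of enrolled children will be selected for the pre-post assessment". Applied to 1500 to 3000 children and their mothers, at one mother per child, that is 150 to 300 mothers. The same section gives the design values: "effect size approximately 0.4-0.5) with 80% power at a 5% significance level in paired measurements".

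**Inputs assumed.** The article gives no attrition figure, so 10%, 20% and 30% missing post scores are used for illustration. The test is taken as two-sided.

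**The article's own figure first.** The paired sample size is n = ((1.960 + 0.842)/d)².

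- d = 0.4: (2.802/0.4)² = 49.1, so 50 pairs.
- d = 0.5: (2.802/0.5)² = 31.4, so 32 pairs.

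A sample of 150 to 300 exceeds both, before any allowance for clustering or dropout. The power statement therefore holds on this basis, and the present point does not depend on it.

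**Size of a possible overstatement.** Let f be the fraction without a post score, 0.4 SD the gain in completers and g the gain in missing mothers. Suppose missing mothers resemble completers on baseline score and covariates. Both missing-at-random analyses then report about 0.40, while the true mean gain is (1 − f) × 0.4 + f × g.

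| Missing fraction f | g = 0.4 (as completers) | g = 0.2 | g = 0 | Overstatement at g = 0: 1/(1 − f) − 1 |
|---|---|---|---|---|
| 10% | 0.40 | 0.38 | 0.36 | 11% |
| 20% | 0.40 | 0.36 | 0.32 | 25% |
| 30% | 0.40 | 0.34 | 0.28 | 43% |

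**Do the two analyses really agree?** Pre and post scores were simulated for 200 mothers in 100 centers, with a true change of 0.40 SD, 400 replicates and 20 imputations. A missing-at-random likelihood estimator stood in for the mixed model.

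- *Missingness depending on the baseline score only (missing at random holds):* both methods had bias near zero.
- *Less-improved mothers more often missing:* bias was +0.09 for both at 10% missing, +0.18 for both at 20% and +0.26 for both at 30%. The mean absolute difference between the two methods was only 0.004, 0.005 and 0.007.
- *Same mechanism, 20% missing, imputed values shifted down by 0.5 SD:* bias fell to about +0.075. The shift moves the estimate by 0.2 × 0.5 = 0.10, which makes the dependence on the assumption visible.
- *Missingness depending only on a recorded variable correlated with the change, such as attendance, 20% missing:* imputation using that variable had bias 0.00, against +0.08 for the likelihood estimator without it.

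The simulated mechanism is severe. At 20% missing the completers' mean change was 0.40 + 0.227 = 0.627, so the missing mothers averaged (0.40 − 0.8 × 0.627)/0.2 ≈ −0.51 SD, which is a decline. The simulation shows that the two methods move together. It does not forecast the bias in this study, and the zero-gain table is the milder illustration.

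**Would significance be lost?** Take the least favorable cell, a gain of 0.28 with 30% missing from 150 mothers, in units of the SD of change and ignoring clustering. Then z = 0.28 × √105 = 2.9 if only the 105 completers carry information, and 0.28 × √150 = 3.4 if all 150 do. Both exceed 1.96. The practical issue is therefore the size of the gain more than its significance.

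**The case against.** The strongest reply is that this is detail for a statistical analysis plan that is not shown. The article states its missing-at-random assumption openly, only says that imputation may be considered, and never says what the imputation will assume. Delta-adjusted imputation is itself multiple imputation and would fit the sentence as written. All of that is fair. What remains is that the article names one specific check, says nothing to take it beyond its standard form, and that form does not test the stated assumption.

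A reader might go further and infer that the estimated improvement *is* biased upward. The documents do not support that. The Discussion speaks of difficulty attending education sessions and does not mention failure to answer the post questionnaire. A mother can miss sessions and still be surveyed, and her low gain is then observed. Eligibility requires being able to attend, contact details are kept for follow-up, sessions are attached to existing contacts, and occupation may absorb part of the work-related absence. No attrition is reported or forecast.

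A reader might also infer that imputation *cannot* reveal such bias. That is too strong, because imputation that uses recorded attendance could expose part of it. The article names no such variable, but it does not exclude one.

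**Conclusion.** The point holds in a limited form. As written, the one sensitivity analysis named would, in its standard form and with the same variables, repeat the main model's assumption, and its agreement with the main result should not be read as evidence of robustness. That the imputation is of the standard kind is an inference, since the article does not state its assumption.

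The possible overstatement is conditional. It is 0.04, 0.08 or 0.12 SD on a reported gain of 0.40 if 10%, 20% or 30% of post scores are missing, missing mothers gain nothing and they otherwise resemble completers. It is smaller if they gain something, and absent if missing at random holds. A statistically significant result would probably survive most of this range with 150 to 300 mothers.

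The Introduction classes knowledge change as secondary and exploratory, and the article makes the proposal for routine adoption depend on implementation outcomes. The consequence is therefore modest, but the correction is easy.

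**What to change.** Replace the sentence on multiple imputation with a specification along these lines:

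- If a non-trivial share of post scores is missing, with the threshold stated in advance, the sensitivity analysis will be delta-adjusted multiple imputation.
- The mean change of mothers with missing post scores will be stepped from the value implied by missing at random down to zero.
- The estimated change and its 95% CI will be reported at every step, separately for knowledge, attitude and behavior. A point at which significance disappears should not be the main output, because it may not occur within the range.
- Standard imputation may stay alongside, with session attendance as an auxiliary variable if it is recorded for the sampled mothers.

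The text should be settled before the post scores are analyzed, which the article schedules for May 2026. The cost is a sentence or two and a few additional runs, with no new data. The downside is a little more analysis work and possibly a less favorable range for a secondary exploratory outcome.
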